#### *Maintenance*

Participants engaged in PSM at the end of follow up will be asked to respond to the following prompt, “I would like to continue PSM following study completion” (Yes, No, or Unsure) and will be given the opportunity to provide comments and/or reasons for their answer. Clinicians at each site will be asked to state whether the participant should be allowed to continue PSM following study completion (Yes, No, Unsure). For “maintenance” outcomes, concordance for continued PSM preference following study completion between patients and clinicians will be assessed using the kappa statistic. A p-value  $< 0.05$  will be considered statistically significant.

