#### **Discussion**

This study is designed to answer an important question regarding the feasibility of warfarin PSM implementation in the US healthcare system. While PSM is recommended as the preferred warfarin management strategy by evidence-based guidelines it is virtually unused in the US healthcare system despite being widely used elsewhere in the world. Our study team members previously identified addressable barriers to and potential facilitators of wider PSM

implementation from the perspective of US patients receiving warfarin and clinicians who manage them. The results of these earlier qualitative studies were used in the rationale and design of the protocol for this implementation study. Our study is intended to demonstrate the feasibility of PSM implementation in the US healthcare system and generate an implementation toolkit for use by others interested in exploring PSM use at their clinical sites.

This study will be among the largest to assess the feasibility of PSM implementation in US settings and the first to use an implementation toolkit specifically designed to address barriers and incorporate facilitators previously identified through qualitative focus groups and interviews with US clinicians and patients, respectively. To our knowledge only three small studies evaluating PSM in the US have been conducted to date. The planned enrollment of 150 patients for our study will exceed that of all previous US-based studies combined.

The proposed study will provide crucial information on the characteristics of patients likely to be interested in attempting PSM, the performance of PSM patient educational tools, the usability of clinical decision support tools, the capability of US patients to safely engage in PSM, and the acceptability of PSM workflows in US healthcare settings.

We chose the RE-AIM framework as it has been shown to highlight essential program elements including external validity that can improve the sustainable adoption and implementation of effective, generalizable, evidence-based interventions like PSM. Further, we chose to utilize anticoagulation management services that have achieved Anticoagulation Centers of Excellence status as defined by the Anticoagulation Forum based on the premise that successful PSM implementation at these sites will promote dissemination of PSM implementation strategies to other centers throughout the US.

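### The kappa planned for Maintenance compares a patient's wish with a clinician's permission, and it can take the same value whether willing patients would be refused or permitted patients would decline

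*Protocol*

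**What the plan says.** All of this stands in the Protocol, Outcomes and Analysis, Maintenance.

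- **Who is asked.** "Participants engaged in PSM at the end of follow up will be asked to respond to the following prompt", so the comparison covers only those still on patient self-management (PSM).
- **Patient item.** "I would like to continue PSM following study completion", answered Yes, No or Unsure, with room for comments and reasons.
- **Clinician item.** "Clinicians at each site will be asked to state whether the participant should be allowed to continue PSM following study completion", with the same three answers.
- **Analysis.** "concordance for continued PSM preference following study completion between patients and clinicians will be assessed using the kappa statistic". A p-value below 0.05 "will be considered statistically significant".

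No other Maintenance analysis is named. The section gives no expected distribution of answers, no kappa value to be reached and no weighting. Elsewhere (PSM implementation phase), preference for continuing PSM appears only as an item in the participant's final survey. No clinician preference is collected.

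**The concern.** The patient says what he or she wants, and the clinician says what should be permitted. The outcome label treats these as one shared preference.

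Because the questions differ, the two kinds of disagreement mean different things. A patient who answers No while the clinician answers Yes is declining something that would be allowed, and the two answers are compatible. A patient who answers Yes while the clinician answers No is in conflict with the clinician over continuing. Both bear on maintenance, but one is patient reluctance and the other is clinician refusal.

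Kappa is symmetric in the two raters and cannot tell them apart. The test at p<0.05 does not help, because it asks only whether agreement exceeds chance. The Discussion expects the study to inform safe engagement in PSM and the acceptability of its workflows. The share of willing patients whose clinician would not allow continuation bears on both, and the one named statistic does not report it.

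**Working it through.** **Inputs.** The protocol states no kappa, expected answers or power for this outcome, so there is no figure to reproduce. Every cell count below is an assumption. The only bound is "The planned enrollment of 150 patients for our study" (Discussion). The number still on PSM at six months is not given, so I use 100, 120 and 150 pairs.

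**Formulas.** With patient margins r_i and clinician margins c_i as proportions:
- Po = sum of the diagonal proportions; Pe = Σ r_i c_i; kappa = (Po − Pe)/(1 − Pe).
- Null standard error = √[Pe + Pe² − Σ r_i c_i (r_i + c_i)] / [(1 − Pe)√n]; z = kappa / standard error.

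Transposing the table swaps r and c. Every term above is unchanged, so kappa and its p-value are too.

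**Step 1: the same disagreements in opposite directions, 100 pairs, no Unsure answers.**

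| | Table A | Table B |
|---|---|---|
| Both Yes | 80 | 80 |
| Patient No, clinician Yes | 15 | 0 |
| Patient Yes, clinician No | 0 | 15 |
| Both No | 5 | 5 |

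In both tables:
- Po = (80 + 5)/100 = 0.85
- Pe = 0.80 × 0.95 + 0.20 × 0.05 = 0.77
- kappa = 0.08/0.23 = 0.348
- Σ r_i c_i (r_i + c_i) = 0.76 × 1.75 + 0.01 × 0.25 = 1.3325
- standard error = √(0.77 + 0.5929 − 1.3325)/(0.23 × 10) = √0.0304/2.3 = 0.076, so z = 4.6

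Both tables count as significant. Willing patients whose clinician says No, with exact (Clopper-Pearson) 95% intervals:
- Table A: 0/80 = 0% (0 to 4.5%)
- Table B: 15/95 = 15.8% (9.1 to 24.7%)

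**Step 2: other assumed sizes.**
- 120 pairs (100 both Yes, 8 both No, 12 disagreements): Po = 108/120 = 0.90, Pe = (112 × 100 + 8 × 20)/120² = 0.789, kappa = 0.526 and z = 6.55, whether the 12 are all patient-Yes/clinician-No or all the reverse.
- 150 pairs (120 both Yes, 10 both No, 5 both Unsure, 15 disagreements): kappa = 0.627 and z = 10.06 in either direction.

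**Step 3: answers all Yes on one side, 120 pairs.**
- All clinicians Yes, 12 patients No: Po = 108/120 = 0.90, Pe = 0.90 × 1 + 0.10 × 0 = 0.90, kappa = 0. No willing patient is refused.
- All patients Yes, 12 clinicians No: kappa = 0 again, now with 12 refusals.
- In both, the null standard error is also zero (0.90 + 0.81 − 0.90 × 1.90 = 0), so the planned test cannot be formed.
- Everyone Yes: Pe = 1 and kappa is 0/0, undefined, although agreement is complete.

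Mostly-Yes answers are plausible, because only people still engaged in PSM are asked.

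**Step 4: limit of the argument.** Keep 120 pairs, 8 both No and no other disagreement, and vary the patient-Yes/clinician-No count:

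| Conflicts | 0 | 3 | 12 | 24 |
|---|---|---|---|---|
| Kappa | 1.00 | 0.83 | 0.53 | 0.33 |

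Kappa does respond to conflict. It does not show that conflict, rather than the reverse disagreement, is what lowered it.

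**The case against.** **Both items concern the same patient, the same event and the same three answers, so agreement between them is a sensible question.** This stands. A reader might infer that the planned kappa is not concordance at all. The protocol does not support that: kappa measures chance-corrected agreement of the coded answers. What it does not measure is agreement on one shared preference.

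**Kappa is not blind to conflict.** This also stands. A reader might infer that kappa is the same whether or not any patient is in conflict with the clinician. Step 4 shows otherwise, and a kappa of 1 excludes conflict. The equality arises when the same disagreements lie in the mirror-image cells. The correct statement is that kappa can coincide.

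**Either direction of disagreement may end PSM, so counting both is defensible.** Fair, and a reason to report both. It is not a reason to merge them in one number, since they have different causes.

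**The cross-table is needed to compute kappa, no decision hangs on the result, and tabulation detail belongs in an analysis plan that is not shown.** No data are lost, and the protocol sets no kappa threshold for sustained PSM, so a wrong programme decision cannot be claimed. But the point is not a missing table. The protocol itself fixes the label, the statistic and the significance criterion, and that choice fits the two items poorly.

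**The illustrations are assumed, one-sided and mostly without Unsure.** True. They show what can happen, not what is likely. The symmetry in Step 1 is algebraic and holds for any 3x3 table.

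**Conclusion.** The point holds in a limited form. The Maintenance section labels a wish and a permission as one preference and names only kappa with p<0.05 to summarise them. That statistic cannot separate clinician refusal from patient reluctance: in the 100-pair illustration, kappa is 0.35 with either 0% or 15.8% of willing patients refused. It is 0 and untestable when exactly one side answers all Yes, and undefined when both do.

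The symmetry needs no assumption about the data. The sizes rest wholly on assumed counts. The consequence is confined to one RE-AIM element: the primary Reach outcome, Effectiveness and Implementation (fidelity) do not use this statistic. The change is worth making because it costs almost nothing, but nothing here threatens the study's main result.

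**What to change.** In the Maintenance section:

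1. Describe the clinician item as a judgement on whether continuation should be permitted, and remove the wording that calls both answers a preference.
2. Make the main summary the 3x3 patient-by-clinician table, with two percentages, each with an exact 95% confidence interval:
   - among patients answering Yes, those whose clinician answers No or Unsure;
   - among pairs in which the clinician answers Yes, those whose patient answers No or Unsure.
3. Keep kappa as supplementary, with its confidence interval instead of a test against zero, and state that it will not be reported when it is undefined.

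Do not reword the clinician item to match the patient's. Enrollment began on March 1, 2023 with a 6-month PSM phase, so a change now could mix two versions of the item. It would also drop the permission judgement that makes the item informative.

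The cost is a few lines of analysis text. Both answers are already collected, so no extra data or participants are needed.

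### Kappa judged at p < 0.05 shows only better-than-chance agreement, so it does not show how well patients and clinicians agree on continuing PSM

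*Protocol*

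**What the plan says.** The Maintenance section (Protocol, Outcomes and Analysis) restricts the patient question to those still self-managing: "Participants engaged in PSM at the end of follow up will be asked to respond to the following prompt". The prompt offers Yes, No or Unsure. The clinician gives a separate judgement on the same three options: "Clinicians at each site will be asked to state whether the participant should be allowed to continue PSM following study completion (Yes, No, Unsure".

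The analysis is one sentence: "concordance for continued PSM preference following study completion" between "patients and clinicians will be assessed using the kappa statistic". The criterion follows directly: "A p-value $< 0.05$ will be considered statistically significant".

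The section does not state a null value, whether the test is two-sided, or a kappa that would count as adequate. The number of pairs is not given either. It cannot exceed the enrolment target in the Discussion ("The planned enrollment of 150 patients for our study") and will be lower if participants leave PSM before the end of follow-up.

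**The concern.** The Maintenance question is how closely patients and clinicians agree on who should carry on with PSM. The usual p-value attached to kappa answers a different question, namely whether agreement exceeds what the two sets of marginal totals would produce by chance. Two people judging the same six months of self-management can be expected to agree better than chance, so rejecting that null says little.

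A second issue depends on the data. Only participants still in PSM are asked, so Yes may dominate on both sides. Kappa then rests on a handful of No and Unsure answers, and its p-value can turn on one or two people.

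At stake is the reading of the only formal analysis named for one of the five RE-AIM elements. Weak agreement could be reported as significant concordance, and a non-significant kappa could hide a table in which almost every pair agrees.

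**Working it through.** **Inputs.** From the protocol: three categories per rater, kappa, p < 0.05, at most 150 pairs. Assumed, because the protocol does not say: unweighted kappa, null kappa = 0, two-sided test, 100 to 150 pairs, 50% to 98% Yes answers with the remainder split equally between No and Unsure. The protocol gives no expected kappa or power for this outcome, so there is no figure of its own to reproduce.

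**Formulas.** With observed agreement po and chance agreement pe = Σ p_i. p_.i:

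- kappa = (po - pe) / (1 - pe)
- null variance: SE0² = [pe + pe² - Σ p_i. p_.i (p_i. + p_.i)] / [n(1 - pe)²]
- z = kappa / SE0, so the smallest significant kappa is 1.96 × SE0

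**Step 1: the smallest kappa that is significant.** For n = 150 and 50% Yes on both sides (25% No, 25% Unsure): pe = 0.25 + 0.0625 + 0.0625 = 0.375. The sum in the variance is 2 × (0.125 + 2 × 0.015625) = 0.3125. SE0² = (0.375 + 0.1406 - 0.3125) / (150 × 0.3906) = 0.00347, so SE0 = 0.059 and 1.96 × SE0 = 0.115. Other cases:

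| Pairs | 50% Yes | 80% Yes | 90% Yes | 95% Yes |
|---|---|---|---|---|
| 100 | 0.141 | 0.150 | 0.153 | 0.154 |
| 120 | 0.129 | 0.137 | 0.139 | 0.140 |
| 150 | 0.115 | 0.122 | 0.125 | 0.126 |

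The threshold is about 0.12 to 0.15 throughout and needs no skew towards Yes. In simulation (20,000 samples per scenario) with true kappa only 0.2 and 50% Yes, the chance of a significant result was 0.91 at n = 150 and 0.78 at n = 100.

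**Step 2: weak agreement that passes.** Rows are patients, columns clinicians, in the order Yes, No, Unsure. Table [[60,18,12],[16,14,5],[12,5,8]], n = 150:

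- po = (60 + 14 + 8)/150 = 54.7%
- pe = (90×88 + 35×37 + 25×25)/150² = 9840/22500 = 0.437
- kappa = (0.547 - 0.437)/(1 - 0.437) = 0.19 (95% CI 0.06 to 0.32)
- SE0 = 0.0605, z = 3.21, p = 0.001

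Agreement specific to No is 2×14/(35 + 37) = 39%, and to Unsure 2×8/(25 + 25) = 32%.

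**Step 3: mostly-Yes answers.** Table [[142,2,2],[2,0,0],[2,0,0]], n = 150:

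- po = 142/150 = 94.7%
- pe = (146² + 2² + 2²)/150² = 21324/22500 = 0.9477
- kappa = -0.02, p = 0.75

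Now change one participant from Unsure (patient) and Yes (clinician) to No from both:

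- po = 143/150 = 95.3%
- pe = (146×145 + 3×3 + 1×2)/150² = 21181/22500 = 0.9414
- kappa = 0.20, p = 0.002, 95% CI -0.16 to 0.57

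One participant reverses the significance statement while raw agreement barely moves. In the second table the p-value and the interval also disagree about zero, because the test uses the null standard error and the interval does not.

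At the extreme, if clinicians say Yes for all 150 and 140 patients say Yes, then po = pe = 93.3% and kappa is exactly 0. If everyone says Yes, kappa is 0/0 and undefined.

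**Step 4: how much skew is needed.** Simulated standard deviation of kappa, true kappa 0.4:

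| Pairs | 50% Yes | 80% Yes | 90% Yes | 95% Yes | 98% Yes |
|---|---|---|---|---|---|
| 100 | 0.076 | 0.107 | 0.148 | 0.215 | 0.324 |
| 150 | 0.063 | 0.087 | 0.119 | 0.169 | 0.276 |

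At 98% Yes and n = 150, about 28% of samples give kappa at or below 0 although mean agreement is 97.7%. At 80% Yes or below the loss of precision is modest.

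**The case against.** Several objections have force.

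- **No pass/fail rule is written.** A reader might infer that p < 0.05 will be declared concordance and anything else its absence. The protocol does not say so. The sentence resembles the significance conventions in the Reach, Effectiveness and Implementation sections, kappa would presumably be reported as a value, and no later decision depends on it. This stands. What remains is that p < 0.05 is the only criterion the section gives for reading the result.
- **The distribution of answers is unknown.** A reader might infer that both sides will answer mostly Yes. The protocol states no expected distribution, and the clinician item is a separate judgement with its own No and Unsure options. Restricting the question to participants still in PSM makes the skew plausible and no more. Steps 1 and 2 do not need it.
- **A kappa near zero is not an error.** A reader might infer that kappa gives a wrong answer when 94.7% of pairs agree. In that table no pair agrees on No or Unsure, so kappa correctly reports no agreement beyond chance on who should stop. The trouble is that a non-significant p-value conveys neither that fact nor the high overall agreement.
- **Reporting detail belongs in an analysis plan.** Tables, intervals and raw agreement may be in a statistical analysis plan that is not shown, and the protocol does not exclude them. Their absence is not the point here. The criterion that the protocol itself fixes is.

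Thresholds worked out from a two-category table should not be carried over. At 120 pairs a Yes/not-Yes table with equal marginal totals on the two sides gives about 0.18, against about 0.13 to 0.14 on the protocol's three-category scale.

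**Conclusion.** The concern holds in limited form. With kappa = 0 as the default null, p < 0.05 establishes only better-than-chance agreement. With 100 to 150 pairs it is reached at a kappa of about 0.12 to 0.15, and a table with 54.7% agreement reaches p = 0.001. This rests on unweighted kappa, a two-sided test and the assumed number of pairs, and not on skewed answers.

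The fragility is conditional. It is marked when Yes answers reach about 95% or more and mild at 80% or below, and the protocol does not tell us which will apply.

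The documents do not support saying that the Maintenance conclusion will be wrong, only that the stated criterion does not measure the degree of concordance. Severity is low: the primary implementation outcome is in Reach, and no sample size or safety conclusion depends on this analysis.

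**What to change.** In the Maintenance section, remove p < 0.05 as the criterion for concordance. Replace it with one sentence: report the 3x3 patient-by-clinician table, overall percent agreement, agreement specific to Yes and to No/Unsure, and kappa, each estimate with a 95% CI. State that kappa is descriptive and that it is undefined if all answers on both sides fall in one category.

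All the data are already collected, so the cost is a wording change. The downside is losing a single significance statement.

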#### **Discussion**

This study is designed to answer an important question regarding the feasibility of warfarin PSM implementation in the US healthcare system. While PSM is recommended as the preferred warfarin management strategy by evidence-based guidelines it is virtually unused in the US healthcare system despite being widely used elsewhere in the world. Our study team members previously identified addressable barriers to and potential facilitators of wider PSM

implementation from the perspective of US patients receiving warfarin and clinicians who manage them. The results of these earlier qualitative studies were used in the rationale and design of the protocol for this implementation study. Our study is intended to demonstrate the feasibility of PSM implementation in the US healthcare system and generate an implementation toolkit for use by others interested in exploring PSM use at their clinical sites.

This study will be among the largest to assess the feasibility of PSM implementation in US settings and the first to use an implementation toolkit specifically designed to address barriers and incorporate facilitators previously identified through qualitative focus groups and interviews with US clinicians and patients, respectively. To our knowledge only three small studies evaluating PSM in the US have been conducted to date. The planned enrollment of 150 patients for our study will exceed that of all previous US-based studies combined.

The proposed study will provide crucial information on the characteristics of patients likely to be interested in attempting PSM, the performance of PSM patient educational tools, the usability of clinical decision support tools, the capability of US patients to safely engage in PSM, and the acceptability of PSM workflows in US healthcare settings.

We chose the RE-AIM framework as it has been shown to highlight essential program elements including external validity that can improve the sustainable adoption and implementation of effective, generalizable, evidence-based interventions like PSM. Further, we chose to utilize anticoagulation management services that have achieved Anticoagulation Centers of Excellence status as defined by the Anticoagulation Forum based on the premise that successful PSM implementation at these sites will promote dissemination of PSM implementation strategies to other centers throughout the US.

This study is registered on ClinicalTrials.gov (NCT04766216) and will be updated with any modifications and results. The outcomes of the study will be presented at scientific meetings and reported in peer-reviewed journals. The data that support the findings of this study

327 will be available from the corresponding author upon reasonable request. Access will be granted  
328 to qualified researchers for the purposes of academic, non-commercial research, in accordance  
329 with institutional and ethical guidelines.

330 Funding

331       This research program is funded by the Agency for Healthcare Research and Quality  
332 (AHRQ) to [name] (Federal Award Identification Number – R18HS027960). Research reported  
333 in this article is supported by the National Center for Advancing Translational Sciences of the  
334 National Institutes of Health under Award #UL1TR002538. The content is solely the  
335 responsibility of the authors and does not necessarily represent the official views of the National  
336 Institutes of Health.

337

338 Conflicts of interest

339 [name] reports serving as a member of the Anticoagulation Forum's Advisory Council.

340 [name] reports serving as a member of the Anticoagulation Forum's Board of Directors, and

341 consulting for Pfizer, Bristol-Myers Squibb, Janssen, Bayer, AstraZeneca, Sanofi, Anthos,

342 Abbott Vascular, and Boston Scientific. [name] reports serving as a member of the

343 Anticoagulation Forum's Advisory Council.

344

Table 1. Stepwise process for developing a warfarin PSM implementation strategy

1. Consider the pros and cons of PSM models used in European healthcare settings.
2. Consider processes used to solve similar problems (e.g., self-management of insulin therapy).
3. Develop an “ideal PSM implementation strategy” wherein anything is possible to achieve successful PSM implementation as a starting point for thinking about potential PSM strategies to test.
4. Move from the ideal to the realistic by highlighting differences between the ideal strategy and PSM implementation barriers identified in prior qualitative studies of patients and clinicians.
5. Consider the relative advantage, compatibility with current processes and beliefs, simplicity of implementation, and trialability of potential PSM implementation strategies.
6. Develop an organized structure to oversee the PSM implementation process and identify key elements that must exist in a successful PSM implementation strategy and elements that can be adapted to meet individual implementation site needs.

345 PSM-patient self-management

346

| Table 2. Screener questions for patients potentially interested in warfarin PSM study participation |                                                                           |
|-----------------------------------------------------------------------------------------------------|---------------------------------------------------------------------------|
| 1.                                                                                                  | Why are you taking warfarin?                                              |
| 2.                                                                                                  | What is your INR goal range?                                              |
| 3.                                                                                                  | What is your warfarin tablet strength?                                    |
| 4.                                                                                                  | What would you do with your warfarin dose if your INR result was too low? |
| 5.                                                                                                  | What bad things could potentially happen if your INR gets too high?       |

347 PSM-patient self-management; INR-international normalized ratio

348

| Table 3. Timing of PSM study data collection |           |            |           |            |            |
|----------------------------------------------|-----------|------------|-----------|------------|------------|
| Study element                                | Pre-study | Enrollment | Weeks 1-4 | Months 1-6 | Post-study |
| Study Coordinator                     |           |            |           |            |            |
| Eligibility determination                    | X         |            |           |            |            |
| Screening questions                          |           | X          |           |            |            |
| Obtain consent                               |           | X          |           |            |            |
| Baseline characteristics                     |           | X          |           |            |            |
| Bleeding/thromboembolic event chart reviews  | X         |            |           |            | X          |
| Pre-study INRs & warfarin doses              | X         |            |           |            |            |
| Patient                               |           |            |           |            |            |
| Baseline survey                              |           | X          |           |            |            |
| Education module                             |           | X          |           |            |            |
| Spotters ready INR surveys                   |           |            | X         |            |            |
| PSM INR surveys                              |           |            |           | X          |            |
| Post-study survey                            |           |            |           |            | X          |

349 PSM-patient self-management; INR-international normalized ratio

350

|                                                                                   |                                                                                                                                                             |
|-----------------------------------------------------------------------------------|-------------------------------------------------------------------------------------------------------------------------------------------------------------|
| [figure not shown] | Recruit prospective PSM patients who were already self-testing INRs using home INR machines                                                          |
| [figure not shown] | Screen potential PSM patients using established patient-clinician relationships                                                                      |
| [figure not shown] | Provide PSM patient education using an interactive online module                                                                                     |
| [figure not shown] | Provide an online data collection form for patients to self-report INR results, warfarin dosing decisions, and bleeding/thromboembolic complications |
| [figure not shown] | Facilitate transition to PSM using a “spotters ready” phase (2-4 weeks) with clinicians until patients confident to fully assume PSM responsibility  |
| [figure not shown] | Utilize remote clinician review of PSM dosing decisions and intervene in situations that could result in patient harm                                |
| [figure not shown] | Regularly assess patient and clinician comfort level with PSM                                                                                        |

Figure 1. Core elements of the organized structure to guide warfarin patient self management implementation. PSM-patient self management; INR-international normalized ratio.

[figure not shown]

Figure 2. Overview of type III implementation-effectiveness hybrid research design. PSM-patient self-management; INR-international normalized ratio; TTR-time in therapeutic INR range

